#### Primary outcome

2.4.1

The primary outcome of this trial is the proportion of participants whose CSBM is ≥3 during weeks 3 to 10 (bowel movements with a sensation of complete evacuation).^[2]^

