### Sample size calculation

2.5

In this trial, pass 11 was used to calculate the sample size. There is an absence of studies on acupressure for chronic FC. The selection of the acupoint and the sham acupoint of our study is the same as that of a previous acupuncture study,^[17]^ as is the primary outcome. In this trial, we wanted to achieve 80% power at a significance level of 0.05. Considering a 10% dropout rate, we need 154 subjects in total and 77 subjects per group.

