### Randomization and blinding

2.6

The participants will be enrolled in the experimental and control groups at a ratio of 1:1. An independent researcher will generate the randomization sequence using SPSS (SPSS 21.0, SPSS Inc., Chicago, IL). The random numbers will then be placed in opaque envelopes, which will be numbered sequentially and sent to the independent researcher in charge of randomization. The envelopes will be opened sequentially according to the numbers. Then, allocation is determined. The former researcher will unmask the envelopes after interviewing; therefore, the participants and other investigators will be blinded to the allocation. Outcome assessors, data managers, and statisticians will be blinded in this trial and will be separated so that they cannot share information. Furthermore, we will set a standard procedure for communication to ensure treatment blinding. The allocation will be revealed once the trial is completed.

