### Date analysis

2.9

SPSS (version 21.0; SPSS Inc., Chicago, IL) will be used in statistical analyses by an independent statistician. Continuous variables will be presented as mean ± standard deviation, while categorical variables will be represented as percentages and numbers. The Chi-square test will be used to assess categorical variables, such as the characteristic and demographic data. The *t* test or Wilcoxon rank-sum test will be used for within- and inter-group comparisons according to the homogeneity and normality analysis. The date of the participant receiving at least one treatment will be included in the analysis. Missing data will be dealt with using the worst-case scenario method. We set the confidence interval to 95%. All tests are 2-tailed, and *P*-values <.05 will be considered to be significantly different.

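### Worst-case handling of missing data is not defined by arm and does not match the dropout allowance in the sample size; power is slightly below 80% on one reading and about 17-25% on the other

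*Protocol article*

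**What the plan says.** Section 2.9 (Date analysis) gives one sentence on missing data: "Missing data will be dealt with using the worst-case scenario method". It does not name an outcome, separate the arms or call the rule a sensitivity analysis. The same section sets the analysis population: "The date of the participant receiving at least one treatment will be included in the analysis". So a participant who starts acupressure and then stops stays in the analysis with imputed values.

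Section 2.5 (Sample size calculation) treats dropout differently: "Considering a 10% dropout rate, we need 154 subjects in total and 77 subjects per group". The design target is "we wanted to achieve 80% power at a significance level of 0.05", and section 2.9 adds "All tests are 2-tailed". The primary outcome in section 2.4.1 is binary: "The primary outcome of this trial is the proportion of participants whose CSBM is ≥3 during weeks 3 to 10". Section 2.5 prints no responder rates. It refers to an earlier trial: "The selection of the acupoint and the sham acupoint of our study is the same as that of a previous acupuncture study".

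**The concern.** The phrase in section 2.9 covers at least two rules that behave very differently.

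- **Differential rule:** a missing outcome is a failure in the acupoint arm and a success in the sham arm. This is an extreme bound, useful for showing how far missing data could move a result. It is not an estimate of the effect.
- **Symmetric rule:** a missing outcome is a non-response in both arms. This is a common and defensible primary analysis for a responder endpoint.

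The same data could support opposite conclusions under the two rules, and the text does not choose between them. Neither rule matches section 2.5, where inflating for dropout implies that those lost are removed from the comparison and the remainder carry the full effect. What is at stake is the stated 80% power, the meaning of the primary estimate and, under the differential rule, the error rate when there is no effect.

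The sentence also covers the continuous outcomes. Taken literally, it puts the end of the scale in place of a missing score.

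**Working it through.** **Inputs from the protocol article.** Two-sided alpha 0.05, 80% power, 10% dropout and 77 per arm (2.5, 2.9); 1:1 allocation (2.6); binary primary outcome (2.4.1); PAC-QOL items scored 0 to 4 (2.4.2.5).

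**Assumptions.** Sham response of 10-20%, with 50% as a further check, because no rate is printed. Missingness is equal in both arms. Dropouts respond like completers.

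**Step 1: the plan's own figure.** 69 / 0.9 = 76.7, which rounds up to 77; also 70 × 1.1 = 77. So 77 corresponds to 69-70 evaluable per arm. The 69-70 itself cannot be reproduced without responder rates.

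**Step 2: effect implied by the design.** Power of the pooled two-proportion test with n per arm is Φ[(|p1 − p2| − 1.96·se0)/se1], where se0 = √(2·p̄(1 − p̄)/n), p̄ = (p1 + p2)/2, and se1 = √([p1(1 − p1) + p2(1 − p2)]/n). Solving for 80% power at n = 69:
- sham 10%: acupoint 28.7%, difference 18.7 points
- sham 20%: acupoint 41.9%, difference 21.9 points

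**Step 3: differential rule, n = 77, missing fraction d.** The expected rates become p1(1 − d) and p2(1 − d) + d.

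| Sham rate | d | Expected rates | Difference | Power |
|---|---|---|---|---|
| 10% | 10% | 25.8% vs 19.0% | 6.8 points | 17% |
| 20% | 10% | 37.7% vs 28.0% | 9.7 points | 25% |
| 10% | 5% | 27.2% vs 14.5% | 12.7 points | 49% |
| 20% | 5% | 39.8% vs 24.0% | 15.8 points | 56% |

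First row in full: p̄ = 0.224, se0 = 0.0672, se1 = 0.0670, and (0.0681 − 1.96 × 0.0672)/0.0670 = −0.95, so power is 0.17.

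**Step 4: differential rule with no true effect, d = 10%.** The expected difference is −10 points at any response rate. For a common rate of 10% (9% vs 19%) sham is significantly better in 43% of trials; for 20% (18% vs 28%), in 31%.

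**Step 5: symmetric rule, n = 77, d = 10%.** The rates become 0.9·p1 and 0.9·p2.
- sham 10%: 25.8% vs 9.0%, power 79%
- sham 20%: 37.7% vs 18.0%, power 78%
- sham 50% (acupoint 73.0% from Step 2): 65.7% vs 45.0%, power 74%

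Under no effect the type I error stays near 5%. A simulation of 200,000 trials per setting agreed with Steps 3 to 5 within about 2 points.

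**Step 6: continuous outcomes.** Take a PAC-QOL mean item score with observed means m1 (acupoint) and m2 (sham), SD s, and 10% missing.
- Filling in 4 in both arms gives means 0.9·m + 0.4. The difference shrinks to 0.9(m1 − m2). The variance becomes 0.9s² + 0.09(4 − m)², which exceeds s² whenever 4 − m is more than about 1.05s.
- Filling in 4 on acupoint and 0 on sham gives a difference of 0.9(m1 − m2) + 0.4, a shift of 0.4 points per item against acupressure. The sham variance becomes 0.9s² + 0.09·m2², which is larger than s² if m2 is more than about 1.05s.

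**The case against.** A reader might infer that the trial has about 20% power and a biased estimate as planned. The document does not support that without conditions, for four reasons.

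1. **The rule is not fixed.** The low power and the false findings for sham belong to the differential reading only. Blinding points somewhat the other way: section 2.6 and the Discussion blind the statistician, and allocation is revealed once the trial is completed. A differential rule cannot be applied without knowing which arm is active, whereas a symmetric one can. This does not settle the matter, since unblinding could come before the analysis.
2. **10% dropout need not be 10% missing on the primary outcome.** Table 1 places randomization in week 1 and treatment from week 3, so losses in the run-in never enter the analysis set. Losses in weeks 11 to 18 come after the primary window. Only losses in weeks 3 to 10 are imputed for that outcome, which is why the 5% rows are shown.
3. **The responder rates are assumed.** Any figure should be read as a range.
4. **Other methods may exist.** The article condenses a fuller plan, and further sensitivity analyses may be specified there. It would be too strong to say that no other method is planned.

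It can also be said that the differential rule errs against acupressure and so cannot produce a false claim of efficacy. That is right as far as it goes, but with two-sided tests it can produce a false claim that sham is better.

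All four points limit the size of the finding. They do not remove it: the stated rule is unqualified, it permits both readings, and section 2.5 matches neither. The continuous-outcome problem in Step 6 arises on either reading if the rule is taken literally, although the article does not spell out the value to be inserted.

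**Conclusion.** The point holds in conditional form. The stated rule leaves open what is imputed in each arm, and the sample size allows for dropout only by inflation.

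With assumed sham response of 10-20% and dropouts who respond like completers, the differential reading gives power of about 17-25% at 10% missing in the primary window and 49-56% at 5%. It biases the estimate against acupressure. With no effect it declares sham better in about 31-43% of trials at 10% missing.

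The symmetric reading gives about 78-79% at equal 10% missing, and about 74% if the sham rate is 50%. On that reading the primary outcome has only a mild problem.

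For continuous outcomes such as PAC-QOL, filling in the scale extreme moves the means and, under the conditions in Step 6, inflates the SD whichever reading is meant.

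The direction of the BSFS scale in section 2.4.2.3 is a separate issue and adds nothing here.

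**What to change.** In section 2.9:
- state that a missing primary outcome counts as non-response in both arms;
- for continuous outcomes, replace scale-extreme filling with a likelihood-based mixed model, or with multiple imputation;
- keep the differential worst case for the primary outcome, labelled as a sensitivity analysis and with the value imputed in each arm written out.

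In section 2.5, restate the power under the chosen rule, together with the responder rates it rests on. With non-responder imputation and equal 10% missing it will be slightly below 80% (about 78-79% for sham response of 10-20%).

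The cost is wording, a slightly lower stated power and a little more analysis work. No extra participants or data are needed if that power is accepted. The choice should be recorded before allocation is revealed.

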## Discussion

3

Chronic constipation has a negative impact on the quality of life, similar to some organic diseases such as diabetes and depression, and places a heavy medical burden on society.^[18]^ Increasing attention is being paid to alternative treatments (such as massage and acupuncture) for constipation, and new therapies are becoming increasingly popular.^[19]^ Acupuncture has been proven to be noninferior to prucalopride in relieving severe chronic constipation in a recent study.^[20]^ However, acupuncture for constipation can be performed only in specialist clinics, making it inconvenient for the patient. Both acupuncture and acupressure are based on meridian theory in Chinese medicine and influence the flow of qi by stimulating acupoints. However, acupressure is not an invasive method and can be performed by the patient at home. As one group of trials contains the sham acupoints, it is impossible to blind the researchers responsible for the teaching of acupressure. Patients will not know what group they are in. We will also blind data managers and the statistician. They will not communicate the trial's outcome. Moreover, the patient will assess the outcome, which is less likely to introduce biases to subjective outcomes.^[21]^ We will not perform the flora analysis due to the limitation of the fund, although it is an ideal way to explore the mechanisms of acupressure for constipation management.

High-quality data will be collected from this randomized, 2-arm parallel, sham-controlled trial to determine whether acupressure is effective for severe chronic FC. We hope that this trial will provide credible evidence for the application of self-acupressure for the management of severe chronic FC.
